**Brasilia**

**January 2019**

**SUMMARY**

**INTRODUCTION:** The hypoglycemic role of some nutrients has been widely discussed in studies that especially evaluated the long-term effect. However, evaluating and discussing the acute glycemic effect of these nutrients is urgent in order to establish possible dietetic management to help patients with diabetes to control hyperglycemia, especially postprandial hyperglycemia. **OBJECTIVE:** To understand the acute glycemic response after the addition of different foods to the breakfast of patients with type 2 diabetes. **MATERIAL AND METHODS:** This is a crossover clinical trial with 22 patients with type 2 diabetes. They will perform a 120-minute glycemic curve after consuming breakfast with different foods showing varied nutritional characteristics and dosages: 3 g of cinnamon powder, 3 g of cinnamon in capsules; 6 g of cinnamon powder; 6 g of cinnamon in capsules; 100 g lettuce; 100 g of tomato; 30 ml olive oil; mixed salad with 50 g of lettuce, 50 g of tomato and 15 ml of olive oil; 150 g of avocado; 15 g of wheat bran; 15 g of chia seeds or 15 g of golden flaxseed flour, in random order. This research project is linked to the Doctoral Program in Health Sciences and Technologies at the Faculty of Ceilândia at the Universidade de Brasília. **EXPECTED RESULTS:** To understand the acute impact on the glycemic response after adding different foods in different dosages to a meal is essential to indicate effective types and quantities to achieve normoglycemia.

**KEYWORDS:** diabetes mellitus, glycemia, cinnamon, dietary fiber, fats.

1. **INTRODUCTION**

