It is known that high fiber consumption for long periods reduces glycemia in patients with diabetes (Silva *et al*, 2013), but the acute glycemic effect after consuming different types of fiber in physiological amounts for a single meal (according to nutritional recommendations) is necessary to indicate the best dietary modification in the rapid search for normoglycemia (SBD, 2017). The consumption of chia, flaxseed, wheat bran and vegetables, such as lettuce, is associated with decrease in blood glucose level, but the their acute effect on postprandial glycemic response has not been studied (Vuksan *et al* , 2017; Boll *et al*, 2016; Gopal *et al*, 2017).

Food sources of healthy fats are also being investigated. Consumption of avocado plus olive oil for 4 weeks reduced blood glucose levels in women with type 2 diabetes. However, the acute glycemic response after consumption of avocado alone or of olive oil, or of olive oil with salad, has not been studied (Lerman-Garber et al, 1994*)*.

It is necessary and urgent to understand which foods and their dosages show a hypoglycemic effect to help patients with type 2 diabetes in the search for more rapid glycemic control. It is also worth highlighting that dietary approaches have a lower risk of intoxication or side effects compared to medications and can help these patients in the constant search for glycemic control, reducing the risk of polypharmacy, drug interactions and adverse effects, such as intoxication.

1. **OBJECTIVES**

**2.1 General:** To understand the acute glycemic response after adding different foods to the breakfast of patients with type 2 diabetes.

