**2.2 Specifics:**

**I)** To measure the glycemic response at times 0/15/30/45/60/90/120 minutes after consumption of the tested meals, which will be:

- Standard breakfast;

- Standard breakfast plus 3 g of cinnamon powder;

- Standard breakfast plus 3 g of cinnamon capsules;

- Standard breakfast plus 6 g of cinnamon powder;

- Standard breakfast plus 6 g of cinnamon capsules;

- Standard breakfast plus 100 g of lettuce;

- Standard breakfast plus 100 g of tomato;

- Standard breakfast plus 30 ml of extra virgin olive oil;

- Standard breakfast plus 115g of mixed salad containing 50 g of lettuce, 50 g of tomato and 15 ml of extra virgin olive oil;

- Standard breakfast plus 150 g of avocado;

- Standard breakfast plus 15 g of wheat bran;

- Standard breakfast plus 15 g of chia seeds and

- Standard breakfast plus 15 g of golden linseed flour;

**II)** – To check the effect of the tested meals on palatability;

**III)** To compare the time-to-time glycemic responses resulting from the evaluated meals and

**IV)** – To analyze the behavior of the curve and the area below the glycemic curve (at times 0/15/30/45/60/90/120 minutes) after consuming tested meals.

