**3.4 Intervention**

The intervention will take place from 05/01 to 08/30/2019.

Participants will measure their capillary blood glucose before leaving home and, if their blood glucose level is lower than 80 mg/dL or higher than 200 mg/dL, they will not participate in the intervention on that day, and another date will be scheduled. Subjects must arrive at the place where the intervention will take place (at the UPA of Núcleo Bandeirante) between 7:00 am and 8:30 am, and fasting for 8 to 11 hours. In the night before, everyone will eat two standard meals (dinner and supper).

In random order, they will be instructed to consume the standard breakfast, or a standard breakfast plus one of the test foods (foods that will be tested: 3 g of cinnamon powder; 3 g of cinnamon in capsules; 6 g of cinnamon powder; 6 g of cinnamon in capsules; 100 g of lettuce; 100 g of tomato; 30 ml of extra virgin olive oil; 115 g of mixed salad containing 50 g of lettuce, 50 g of tomato and 15 ml of extra virgin olive oil; 150 g of avocado; 15 g of wheat bran; 15 g of chia seeds or 15 g of golden flaxseed flour), within 15 minutes. After consuming each meal, participants will complete the Visual Analogue Scale (**ANNEX II**) to assess palatability, considering appearance, smell, texture, flavor and intensity of flavors (sweet, salty, bitter and sour) (Flint *et al.* , 2000). The glycemic curve will be monitored for 120 minutes at times 0, 15, 30, 45, 60, 90 and 120 minutes. Capillary blood glucose determination will be carried out using the Accu-Check Active device (Roche Diagnostics) made available by the researcher and will be the option of choice so that glycemic results are known quickly and the patient is not exposed to the risk of unmonitored hypoglycemia. The positive area formed below the glycemic response curve will be calculated using the trapezoidal method. Washout application will be for a minimum of 3 days and a maximum of 10 days.

Table 1 presents the nutritional information of the standard breakfast that will be offered to patients. The nutritional value corresponds to approximately 15% of the total energy value of a standard diet of 2,000 kcal, containing 59.4% carbohydrates, 28.6% lipids and 12.0% proteins and is in accordance with the Brazilian Diabetes Society Guidelines (2017).

Table 1. Nutritional information for the standard breakfast

| **Food** | **Quantity** | **CHO (g)** | **LIP (g)** | **PTN (g)** | **Fibers (g)** | **Lime** |

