**3.5 Statistical Analysis:**

Sample characterization data and meal palatability will be analyzed using the mean ± standard deviation. To compare the average palatability scores, the Shapiro- Wilk test will be applied.

To examine the effects of the tested meals and time on blood glucose, two-way analysis of variance (ANOVA) with repeated measures will be performed with *post hoc* comparisons using the Bonferroni adjustment.

The areas under the glycemic curve (AUC) will be calculated using the trapezoidal method, considering the area above baseline values (Tosh, 2013). The Shapiro-Wilk, Levene and Mauchly tests will be applied to assess whether the data present normal distribution, homoscedasticity and sphericity, respectively. The effect of the tested meals on glycemic AUC or appetite scores will be measured by one-way ANOVA with repeated measures with Bonferroni *post hoc comparisons* .

The tests will be carried out using the SPSS Statistics software version 21.0 (IBM Corporation) with a significance level of 5% being accepted.

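### The Bonferroni post hoc comparisons of 13 meals name no contrasts; read as all 78 pairs, they cost each food substantial power against the standard breakfast

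*Protocol*

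**What the plan says.** Section 3.5 plans two repeated-measures analyses of glucose. For the AUC: "The effect of the tested meals on glycemic AUC or appetite scores will be measured by one-way ANOVA with repeated measures with Bonferroni". The adjustment there is applied post hoc. For glucose by meal and time it plans a two-way ANOVA with post hoc "comparisons using the Bonferroni adjustment". Both are run "with a significance level of 5% being accepted". The section does not list the pairs, name a comparator, or say whether the adjustment runs within each time point or over all of them.

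Section 3.4 sets the number of meals: "In random order, they will be instructed to consume the standard breakfast, or a standard breakfast plus one of the test foods". With the 12 test foods listed there, that makes 13 meals. It also sets the times: "The glycemic curve will be monitored for 120 minutes at times 0, 15, 30, 45, 60, 90 and 120 minutes".

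The general objective (section 2.1) is "To understand the acute glycemic response after adding different foods to the breakfast of patients with type 2 diabetes". Specific objective III (section 2.2) is broader: "To compare the time-to-time glycemic responses resulting from the evaluated meals". The Summary says that understanding the response to different foods and dosages "is essential to indicate effective types and quantities to achieve normoglycemia".

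Section 3.2 derives 19 participants from a cited crossover study, adds 15% for losses to reach 22, and mentions a 5% level. It gives no effect size, standard deviation, power or adjusted alpha.

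**The concern.** A Bonferroni post hoc procedure with no named contrasts ordinarily covers every pair of factor levels. With 13 meals, 12 of the 78 pairs compare a food with the standard breakfast and 66 compare two test foods. Some of those 66 have a rationale in the protocol, such as 3 g versus 6 g of cinnamon or powder versus capsule. Others, such as tomato versus chia, have none, yet each costs the same alpha as chia versus the standard breakfast.

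The design and the stated benefit (section 3.7: finding foods that lower glucose acutely) put the weight on what each food adds to the standard breakfast. Spreading alpha over all pairs makes a real reduction harder to detect there. A food could then be reported as showing no difference because of comparisons that nobody had a reason to make.

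The four cinnamon meals form a 2×2 layout of dose and form. Unlisted pairwise tests do not use that structure.

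**Working it through.** **Inputs from the protocol.** 13 meals and 7 times (sections 2.2 and 3.4); 5% level (section 3.5), taken as two-sided; 19 participants before and 22 after the allowance for losses (section 3.2).

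**The plan's own figure.** 19 × 1.15 = 21.85, rounded up to 22, so the inflation step reproduces. The 19 cannot be reproduced because its inputs are not given.

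**Number of comparisons and alpha per test.**
- All pairs: 13 × 12 / 2 = 78; 0.05/78 = 0.00064.
- Against the standard breakfast: 12; 0.05/12 = 0.00417.
- With two cinnamon contrasts added: 14; 0.05/14 = 0.00357.

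**Assumption for power.** Suppose 19 participants give 80%, 90% or 95% power in one two-sided paired t-test at 5%. Solving for the standardised within-pair difference dz gives 0.680, 0.787 and 0.875.

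**Formula.** Power = P(T > t(1 − α/2; df)), where T is noncentral t with noncentrality dz × √n. For a paired test df = n − 1. For a pooled ANOVA error term df = 12(n − 1), which requires sphericity.

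**One case in full.** With dz = 0.680 and n = 22, the noncentrality is 0.680 × √22 = 3.19 on 21 df. The critical value is 3.21 for 12 comparisons and 4.01 for 78, giving power of 51% and 26%.

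**Power per food against the standard breakfast, n = 22**

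| 19 set for | error term | 1 test | 12 tests | 78 tests | ratio 78/12 |
|---|---|---|---|---|---|
| 80% | paired | 86% | 51% | 26% | 0.51 |
| 90% | paired | 94% | 68% | 41% | 0.61 |
| 95% | paired | 97% | 80% | 55% | 0.69 |
| 80% | pooled | 89% | 62% | 40% | 0.64 |
| 90% | pooled | 96% | 79% | 59% | 0.75 |
| 95% | pooled | 98% | 89% | 74% | 0.84 |

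With only 19 completers and dz = 0.680, the paired figures are 80%, 41% and 18% for 1, 12 and 78 tests.

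**Cost of keeping the cinnamon questions.** Bonferroni over 14 instead of 12 (paired, n = 22, 80% case) gives 48% instead of 51%, or 48.2% against 50.5% before rounding: about 2 points. Holm does at least as well.

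**Dunnett, like for like.** On pooled error at n = 22 in the 80% case, a simulated Dunnett critical value of about 2.78 gives 66%, against 62% for Bonferroni over 12 and 40% over 78.

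**Cinnamon 2×2.** With equal within-participant error variance σ², a single pair has variance 2σ². A main effect averaged over the other factor has variance 4 × σ²/4 = σ². The standard error falls by 1 − 1/√2 = 29%.

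**The case against.** **The protocol does not restrict itself to comparisons with the standard breakfast.** Objective III compares the evaluated meals with one another. The Summary wants types and quantities, and the Introduction raises fiber type and cinnamon dose and form. This stands. A reader might infer that the only question is 12 foods against the standard breakfast, but the text does not support that. The weight lies there, and the fix must leave room for food-versus-food contrasts.

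**The 78 pairs are inferred.** Section 3.5 never gives that number. This is correct as a matter of text, but all pairs is what the wording ordinarily means for the AUC.

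**Power is not shown to be more than halved.** A reader might infer this from the case of 19 completers at dz = 0.68 (18/41 = 0.45). At the planned 22 the same case gives 0.51, and larger effects or a pooled error term give 0.61 to 0.84. The protocol supplies no effect size with which to choose among them. Nor should the 26% from a paired test be set against the 66% from a pooled Dunnett test: on the same error term the gain is from 40% to 66%.

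**Error inflation over time is not established.** Adjusting separately at each of 7 times could bring overall error up to 1 − 0.95^7 = 30%, but only if the times were independent. Values on one curve are not, and the text does not say that the adjustment is made per time. Adjusting over all times as one family would give 7 × 78 = 546 tests at 0.000092 each. That controls error but leaves 10% power (paired, n = 22, 80% case).

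**All-pairs Bonferroni controls familywise error.** This also stands. Moreover, much of the loss comes from testing 12 foods at all: at n = 22 in the 80% case, going from one test to 12 already takes power from 86% to 51%.

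**Conclusion.** The point holds as a matter of efficiency. Section 3.5 commits to Bonferroni post hoc comparisons without naming contrasts. On the usual reading this spends alpha on 78 pairs where about 12 to 14 carry most of the trial's purpose. At 22 participants the cost per food is 25 to 27 percentage points with paired tests and 15 to 22 with a pooled error term, over the range in which 19 participants give 80% to 95% unadjusted power. These figures rest on that assumption, on two-sided tests and, for the pooled rows, on sphericity.

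The planned AUC analysis is valid but wasteful, so this is a cheap improvement and not a must-fix. Rewording does not cure the sample size: at dz = 0.68, 80% power needs 34 participants for 12 Bonferroni comparisons and 45 for 78, against the 22 planned.

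**What to change.** In section 3.5, pre-specify the confirmatory family for the glycemic AUC:
- the 12 contrasts of test meal minus standard breakfast;
- two cinnamon contrasts: 6 g versus 3 g averaged over form, and powder versus capsule averaged over dose;
- any other food-versus-food contrast the sponsor needs for objective III, listed by name.

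Use Holm over the whole family, or Dunnett for the 12 contrasts with the standard breakfast, and report differences with adjusted 95% intervals. Report the remaining pairs and the post-baseline time-point comparisons as secondary, with estimates and intervals. Leave out time 0, where no meal effect can exist.

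The cost is wording only. Two extra contrasts take about 2 points of power, and each further listed contrast takes a little more. Unlisted food-versus-food pairs become descriptive, and the two cinnamon main effects average over any dose-by-form interaction.

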**3.6 Risk assessment:**

The risks arising from participating in the research are: to show any gastrointestinal symptoms or variations in blood glucose, including hypoglycemia. However, the volunteers' blood glucose will be constantly monitored and, if there is any complication, they will be directed to the Emergency Care Unit that operates in the same location (UPA Núcleo Bandeirante).

**3.7 Benefits:**

The main benefit of this research is to understand potential foods with an acute hypoglycemic effect that can help patients with diabetes in the search for normoglycemia.

**3.8 Conflicts of interest:**

The researcher reports that there is no conflict of interest.

Data collection will take place outside [name]'s working hours.

**ANNEX I**

**QUESTIONNAIRE FOR INITIAL INTERVIEW**

**I) Personal data** : Date: _____/_____/______

1- Name: ________________________________________________________________________________

2- Address: _____________________________________________________________________________

3- Telephone: _________________________________ Cell phone: __________________________________

4- Date of birth: _____/_____/_________ Age: _____________________________________

5- Email: ________________________________________________________________________________

**II) Anthropometric Data**

6- Weight: ______________________________________________________________________________

7- Height: ________________________________________________________________________________

8- BMI: ______________________________________________________________________________

9- Waist Circumference: _____________________________________________________________

10- You smoke:

( ) Yes

( ) no

( ) others: ________________________________________________________________________

11- Uses medicines/medicines:

( ) no

( ) Yes

Which/at what times/dosage: ______________________________________________________

_____________________________________________________________________________________

_____________________________________________________________________________________

_____________________________________________________________________________________

12- Do you have any allergies or food intolerances:

( ) no

( ) Yes

If yes, which food(s): ___________________________________________________________

_____________________________________________________________________________________

_____________________________________________________________________________________

13- You have good tolerance to the following foods:

- Peach nectar su fresh ( ) Yes ( ) No ( ) I don't know the product

- Industrialized toast ( ) Yes ( ) No ( ) I don't know the product

- Processed cheese ( ) Yes ( ) No ( ) I don’t know the product

- Wheat bran ( ) Yes ( ) No ( ) I don’t know the product

- Passion fruit peel flour ( ) Yes ( ) No ( ) I don't know the product

- Seaweed gelatin powder ( ) Yes ( ) No ( ) I don't know the product

14- Regarding the functioning of your intestine, it is:

( ) regular

( ) irregular

( ) hard stools

( ) excess gas formation

( ) diarrhea

( ) Others: __________________________________________________________________________

15- How many hours do you sleep per night: ______________________________________________________

16- What time do you generally wake up at: _______________________________________________

And what time will you go to sleep: _____________________________________________________________________

17- Do you believe that the quality of your sleep is:

( ) Good ( ) Bad

18- Do you have a sleep disorder or use sleeping medication?

( ) No ( ) Yes Which one(s)? _____________________________________ ___________________

19- Your sleep is:

( ) Continuous

( ) Intermittent

If you wake up during the night, for what reason and how many times: __________________________

_____________________________________________________________________________________

20- You have the habit of consuming breakfast (meal with ≥ 100 Kcal ingested, within 2 hours of waking up, on ≥ 4 days of the week ):

( ) Yes No

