**3 . MATERIAL AND METHODS**

**3.1 Experimental design:** the research is designed as a *crossover clinical trial* .

3.2 Description and selection of the population and sample: 22 subjects with type 2 diabetes treated at the Health Centers of Núcleo Bandeirante, Riacho Fundo I or Candangolândia will participate in this study. They will be invited to participate by putting up posters and giving lectures to publicize the study that will take place at the UPA of Núcleo Bandeirante. The sample size was defined considering the results of the study of De Carvalho *et al.* (‎2017) and the calculation was made by the *G Power* program version 3.1.9.2 (University of Düsseldorf, Germany), which indicated the need for at least 19 participants in each experimental group, to which we added 15% to compensate for possible losses. A significance level of 5% was adopted.

The inclusion criteria will be: to have a diagnosis of type 2 diabetes (American Diabetes Association , 2017); age between 30 ≥ and < 60 years; to consume breakfast regularly (≥ 100 kcal ingested, within 2 hours after waking up, on ≥ 4 days of the week); to be not allergic to the foods tested/used in the study; to agree to eat all study foods; to report no sleep disorders or use sleeping medication; to have availability of time to participate in all meetings within a period of up to 3 months and to agree to participate in the research by signing the Free and Informed Consent Form (TCLE).

Subjects that will be excluded from the study are those who: use exogenous insulin or medications for pathologies other than DM2; have complications from diabetes; smoke; have gastrointestinal disorders or irregular intestinal rhythm; have psychiatric disorders with impaired understanding; participate in other research protocols; refuse to provide or are not able to provide relevant data to the research and who do not attend previously scheduled tests for three times after confirming their presence in the day before the intervention.

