3.3 Initial interview

Volunteers will participate in an initial interview to collect the following data: age, education, anthropometry, smoking, time since diabetes diagnosis, use, type and dosage of medications, presence of allergy and/or food intolerance, intestinal function, number of hours of sleep and self-reported sleep quality, breakfast and fiber consumption habits (**ANNEX I**).

Body weight will be determined using a digital electronic scale and height will be measured using a vertical anthropometer. The body mass index (BMI) value will be calculated and classified according to the recommendations of the World Health Organization (WHO, 2003) . Waist circumference will be measured by determining the midpoint between the lowest rib and the iliac crest, with a flexible and inelastic measuring tape (Heyward & Stolarczyk, 2000). Participants will also undergo body composition assessment using the double emission X-ray densitometry (DEXA) method before and after the end of the intervention.

Volunteers will be instructed to follow individualized nutritional prescriptions, to abstain from alcohol and physical exercise in the 24 hours prior to participating in the research.

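### The data forms contradict the methods: the Annex I tolerance checklist fits other foods and three baseline items are absent, while Annex II shows Saltiness twice and no bitterness

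*Protocol*

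**What the plan says.** **Foods.** Section 3.4 of the Protocol adds one of twelve test portions to the standard breakfast. Four of them are cinnamon ("3 g of cinnamon powder; 3 g of cinnamon in capsules; 6 g of cinnamon powder; 6 g of cinnamon in capsules"). Three more are a single vegetable or oil ("100 g of lettuce; 100 g of tomato; 30 ml of extra virgin olive oil"), and one is a salad that mixes those three. The remaining four are "150 g of avocado; 15 g of wheat bran; 15 g of chia seeds or 15 g of golden flaxseed flour".

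**Eligibility.** Section 3.2 requires participants "to be not allergic to the foods tested/used in the study; to agree to eat all study foods".

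**Initial interview.** Section 3.3 says the interview, on the Annex I form, will "collect the following data: age, education, anthropometry, smoking, time since diabetes diagnosis" and further variables, ending with breakfast and fiber habits. Item 12 of Annex I asks openly about any allergy or intolerance and leaves space to name the food. Item 13 then asks about tolerance of six named products, among them "Passion fruit peel flour ( ) Yes ( ) No" and "Seaweed gelatin powder ( ) Yes ( ) No".

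**Palatability.** Specific objective II in section 2.2 concerns palatability. Section 3.4 says the Annex II visual analogue scale, completed after each meal, covers appearance, smell, texture, flavor and "intensity of flavors (sweet, salty, bitter and sour". The intensity labels shown in Annex II are Sourness, Saltiness, Saltiness and Sweetness.

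**The concern.** These are the trial's own collection instruments. If they are used as printed, what is collected will differ from what the methods promise, and a statistical analysis plan cannot repair that.

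Item 13 adds something that item 12 does not. It lets a participant answer that the product is unfamiliar, and someone who has never eaten a food cannot report an intolerance to it. That prompt is aimed at two products no participant will be given and misses most of those every participant must eat. An intolerance found partway through the 13 meals could cost a participant in a repeated-measures comparison, and section 3.2 enrols 22 against a requirement of 19.

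On palatability, a flavor rating not taken at a visit cannot be reconstructed, and the same form is used after every meal.

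**Working it through.** No sample size, power or alpha figure is involved. The check sets the forms beside the methods and counts.

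**1. Item 13 against the meals.** The twelve test portions in section 3.4 come from eight distinct foods: cinnamon, lettuce, tomato, olive oil, avocado, wheat bran, chia and golden flaxseed. Item 13 lists six products:

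| Item 13 product | Place in this trial |
| --- | --- |
| Peach nectar | Standard breakfast (fruit juice, Table 1) |
| Toast | Standard breakfast |
| Processed cheese | Standard breakfast |
| Wheat bran | Test food |
| Passion fruit peel flour | None; appears nowhere else in the Protocol |
| Seaweed gelatin powder | None; appears nowhere else in the Protocol |

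So 3 + 1 + 2 = 6. Test foods not asked about: 8 − 1 = 7. Test meals with no added food on the checklist: 12 − 1 = 11, since only the wheat bran meal contains wheat bran.

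**2. Annex I against section 3.3.** Items run from 1 to 20 without a gap, and Annex II follows directly. Most variables have a place: age (item 4), anthropometry (6 to 9), smoking (10), medication (11), allergy and intolerance (12), intestinal function (14), sleep (15 to 19) and breakfast habit (20). Education, time since diabetes diagnosis and fiber habits have none. The continuous numbering makes lost text an unlikely explanation.

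**3. Annex II against section 3.4.**

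| Flavor in section 3.4 | Labels in Annex II |
| --- | --- |
| Sweet | 1 (Sweetness) |
| Salty | 2 (Saltiness, twice) |
| Bitter | 0 |
| Sour | 1 (Sourness) |

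The block shows four Weak and four Strong anchors, hence four scales, with 1 + 2 + 0 + 1 = 4 labels. Labels and anchors balance, so a label dropped in reading the drawn form is unlikely. The other palatability block is also complete: four labels (smell, pleasantness, texture, visual appeal), each with its pair of anchors.

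**4. Hunger and fullness scales.** Annex II also carries these, untranslated. Sections 2.2 and 3.4 mention only palatability, but section 3.5 plans a one-way repeated-measures ANOVA of appetite scores. The scales therefore serve a planned analysis that the objectives and procedures do not name.

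**The case against.** The strongest reply is that these are clerical leftovers with little consequence. Several parts of it stand.

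- A reader might infer that only one of eight test foods is screened at all. The Protocol does not support that. Item 12 covers any allergy or intolerance, section 3.2 requires no allergy to the study foods and agreement to eat them all, and it excludes people with gastrointestinal disorders. The count of one in eight describes the item 13 checklist only.
- A reader might infer that safety is compromised or that dropout will rise. The Protocol gives no figure for how many intolerances item 12 and the criteria would miss. Section 3.6 names gastrointestinal symptoms as a risk and places emergency care at the same site, and section 3.2 adds 15% for losses.
- A reader might infer that the three baseline variables are lost. They can be asked at any later visit. Section 3.5 uses characterization data descriptively and names none of them as a covariate.
- A reader might infer that bitterness was certainly not measured. Annex II is a drawn form read as loose text and is partly untranslated, so the wording participants saw is not established. The duplicate may be a translation slip in this version.
- Removing the hunger and fullness scales as strays would be wrong, because section 3.5 analyses appetite scores.

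What the reply does not remove is the contradiction itself. The item 13 and missing-item parts rest on plain text, and the printed flavor labels disagree with section 3.4.

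**Conclusion.** The mismatch is real and worth correcting, with limited reach. Item 13 names two foods foreign to the trial and omits seven of the eight distinct test foods, leaving those to an open question and general criteria. Three variables promised in section 3.3 have no item on the form, and this is recoverable. One of the four flavor intensities required by section 3.4 has no labelled scale in Annex II as shown. If the fielded form matches, bitterness would go unrecorded at each meal and could not be filled in afterwards.

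The Annex II part assumes that this version reflects the form in use; the balance of labels and anchors supports that but does not prove it. The Annex I parts need no such assumption. Nothing here bears directly on glycemic AUC, the sample size or the significance level.

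**What to change.** 1. In Annex I, item 13, replace passion fruit peel flour and seaweed gelatin powder with cinnamon, lettuce, tomato, olive oil, avocado, chia and flaxseed. Keep wheat bran and the breakfast products.
2. Add items to Annex I for education, time since diabetes diagnosis and fiber habits.
3. Check the Annex II form actually given to participants. If it repeats Saltiness, relabel one of the two scales Bitterness; if only the translation is wrong, correct the Protocol copy.
4. Keep the hunger and fullness scales, and name appetite in sections 2.2 and 3.4 so that the analysis in section 3.5 has a stated objective and procedure.

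The cost is one form revision before the first visit and about a minute more per interview.
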